## Methods and analysis

### Objectives

The primary objective of the MELD-ATG (rabbit) (MELD-ATG) trial is to first determine the changes in stimulated C-peptide response over the first 2 hours of an MMTT at 12 months for the 2.5 mg/kg ATG arm versus placebo in paediatric, adolescent and adult people with new-onset T1D.

Conditional on finding a statistical difference between the 2.5 mg/kg ATG arm and placebo, the primary objective is also to identify the minimally effective dose (lowest dose significantly different from placebo) among the doses studied in the trial using change in stimulated C-peptide response over the first 2 hours of an MMTT at 12 months versus placebo.

The secondary objectives are to determine the effects of ATG treatment on (1) stimulated C-peptide (baseline, 3, 6, 12 months), (2) HbA1c (baseline, 3, 6, 12 months), insulin requirements throughout the study, (3) time in range by intermittent CGM (3, 6 and 12 months) measures, (4) fasting and stimulated DBS C-peptide measurements (monthly), (5) mediating a reduction in CD4-positive T cells by relative preservation of CD8-positive T cells and (6) a descriptive analysis of the safety and pharmacodynamic activity profile of different low doses of ATG in different age groups. The exploratory objectives are to study the effects of low doses of ATG treatment on biomarkers related to immunological changes and β-cell death/survival in this population.

Table 1 reports the specific trial objectives and related outcome measures.

**Table 1 T1:** Study objectives and outcomes

Objectives	Outcome measures	Time point(s) of evaluation of this outcome measure
Primary objectives		
1. To determine the changes in stimulated C-peptide response over the first 2 hours of an MMTT for 2.5 mg/kg ATG arm vs the placebo.	1. The area under the stimulated C-peptide response curve over the first 2 hours of an MMTT for the 2.5 mg/kg ATG and placebo arms	1. 12 months
2. Conditional on finding a statistical difference between the 2.5 mg/kg ATG arm and placebo, to identify the minimally effective dose significantly different to placebo among the doses studied in the trial using change in stimulated C-peptide response over the first 2 hours of an MMTT vs placebo	2. The area under the stimulated C-peptide response curve over the first 2 hours of an MMTT for the 0.1 mg/kg ATG, 0.5 mg/kg ATG, 1.5 mg/kg ATG, 2.5 mg/kg ATG and placebo arms	2. 12 months
Secondary objectives		

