### Statistical methods for primary analyses

The primary endpoint, the area under the C-peptide curve over the first 2 hours (using all available measurements within the first 2 hours) of an MMTT (AUC C-peptide) at 12 months (after transformation) will be analysed using a linear regression model at the end of the trial. The model will have fixed effects of time and categorical dose along with an interaction term between time and dose with participant as a random effect and the baseline measurement of MMTT AUC C-peptide (transformed using the ln(x+1) function). The primary contrast of interest is the mean difference in transformed MMTT AUC C-peptide between dose level 2.5 mg/kg and placebo with a 95% CI. The statistical test will be the Wald test or t-test on the 2.5 mg/kg parameter in the model and significance is assessed at the 5% level. If there is a significant effect for the 2.5 mg/kg versus placebo mean difference, then every other dose level will be compared with the placebo dose at the 5% level using t-tests. If there is not a significant effect for the 2.5 mg/kg dose, then no other tests will be carried out. This forms a closed testing procedure for the primary endpoint and the family wise error rate is controlled at 5%. The lowest dose below 2.5 mg/kg that is found to be statistically significantly different to placebo will be declared the minimally effective low dose (MELD).

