### Number of participants to be enrolled: sample size calculation

The SD used for this calculation for the AUC C-peptide endpoint after an MMTT over 2 hours at 12 months was 0.27 nmol/L/min as per^34^; this SD was also estimated as 0.264 nmol/L/min using a data extract from INNODIA from February 2 2020, using the transformed AUC C-peptide value and restricting the extract population to those 5–25 years old. With this SD, 90% power, and 5% significance level, then 32 participants per arm will be needed to detect a change of 0.22 nmol/L/min comparing the 2.5 mg/kg arm to placebo on the transformed ln(AUC C-peptide +1) scale using a two sided two-sample t-test power calculation. Then if this test was significant, there would be 80% power if there were 30 participants (the exact number is unknown but is likely to be fewer than on the 2.5 mg/kg arm) on each middle dose (not 2.5 mg/kg) to detect a change of 0.2 nmol/L/min when comparing to the placebo arm. The sequential testing, that is, a closed testing procedure, means that the familywise error rate of 5% is controlled.

Using the INNODIA mean value of AUC C-peptide, from 175 participants in the longitudinal study aged 5–25 years old, of 0.77 nmol/L/min we would expect to observe a mean difference of 0.42 nmol/L/min between 2.5 mg/kg and the placebo group, while on the transformed scale we would be observe 0.22 nmol/L/min. All tests are superiority tests and the tests are two-sided tests.

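### Testing every lower dose at an unadjusted 5% after the 2.5 mg/kg gate is not a closed test, so familywise error is not held at 5% and can reach about 11–14%

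*Protocol article*

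**What the plan says.** The section on statistical methods for primary analyses sets two steps. First, 2.5 mg/kg is compared with placebo and "significance is assessed at the 5% level". If that test fails, testing ends: "If there is not a significant effect for the 2.5 mg/kg dose, then no other tests will be carried out". If it succeeds, "every other dose level will be compared with the placebo dose at the 5% level using t-tests". No order, adjustment or intersection test is given for the lower doses. The section concludes: "This forms a closed testing procedure for the primary endpoint and the family wise error rate is controlled at 5" per cent. The sample size section repeats it: "a closed testing procedure, means that the familywise error rate of 5% is controlled".

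The dose is then chosen as follows: "The lowest dose below 2.5 mg/kg that is found to be statistically significantly different to placebo will be declared" the MELD. The doses between it and 2.5 mg/kg do not have to be significant.

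The Objectives section makes this part of the primary objective. Conditional on success at 2.5 mg/kg, the trial is to "identify the minimally effective dose (lowest dose significantly different from placebo) among the doses studied in the trial".

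**The concern.** A gate on 2.5 mg/kg protects the lower-dose comparisons only while 2.5 mg/kg is ineffective. The trial is powered at 90% for the opposite case. There the gate usually opens, and what follows is up to three parallel tests at 5% each.

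A closed procedure rejects one dose's null only if every joint null containing it is rejected by a valid 5% test. The gate supplies that test only for joint nulls that include 2.5 mg/kg.

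The second half of the primary objective is at stake. Because the MELD is the lowest significant dose whatever happens above it, one false positive at an inactive dose is enough to name that dose, and the report would carry a 5% assurance that the procedure does not give.

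**Working it through.** **Inputs from the protocol.** SD 0.27, effect 0.22 and 32 per arm for 2.5 mg/kg versus placebo, two-sided 5%, 90% power; effect 0.20 with 30 participants for a middle dose, 80% power. Total 114. Placebo receives 6 + 3 + 3 + 5 + 5 + 5 + 5 = 32 over the seven cohorts, and 2.5 mg/kg the same. That leaves 114 − 64 = 50 for 1.5, 0.5 and 0.1 mg/kg, with at least 6 each from cohort 1.

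**Assumption.** The split of the 50 is decided during the trial, so several splits were tried, from 17/17/16 to 38/6/6 and 6/38/6.

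**Step 1: the plan's power figures.** The noncentrality is δ / [SD·√(1/n₁ + 1/n₂)].
- 2.5 mg/kg: 0.22 / [0.27·√(2/32)] = 3.26, t-test power 89.4% (normal approximation 90.3%). The 32 per arm reproduces.
- Middle dose, 30 versus 32: 0.20 / [0.27·√(1/30 + 1/32)] = 2.91, power 81.8%; with 30 versus 30, 80.5%. The 80% reproduces.

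**Step 2: which joint nulls have a valid test.** Four dose nulls form 15 non-empty combinations. Eight contain 2.5 mg/kg and are covered by the gate. Three are single lower doses tested at 5%. The other four (three pairs and one triple of lower doses) have no test of their own. The rule in effect rejects each of them if any member has p < 0.05. Under independence that has size 1 − 0.95² = 9.75% for a pair and 1 − 0.95³ = 14.3% for the triple. The shared placebo arm lowers these somewhat, but not to 5%.

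**Step 3: familywise error of the stated rule.** Simulation with 400,000 runs per scenario, a shared placebo arm, pooled SD, two-sided t-tests and the stated gate. Ranges are over the splits.

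| Truth | Any false rejection, two-sided | False benefit only (nominal 2.5%) |
|---|---|---|
| 2.5 mg/kg effect 0.22, three lower doses null | 11.1–11.6% | 6.7–6.8% |
| 2.5 mg/kg so effective that the gate always opens, three null | 13.4–13.8% | 6.8–7.0% |
| 2.5 mg/kg 0.22 and 1.5 mg/kg 0.20, two null | 7.6–8.4% | 4.6–4.8% |
| 1.5 and 0.5 mg/kg also 0.20, only 0.1 mg/kg null | 4.0–4.4% | 2.4–2.5% |
| 2.5 mg/kg null | 5.0% | – |

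In the last row any false rejection first needs a false rejection at 2.5 mg/kg, so the gate caps the error. With one null lower dose and a gate that always opens, the two-sided figure is 5.0%. The stated 5% therefore holds in the last two rows and fails in the first three.

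**Step 4: alternatives after the same gate.** With three null lower doses, Holm gives 3.7–4.9% and a fixed descending sequence 3.9–5.0%, depending on the 2.5 mg/kg effect.

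**The case against.** The strongest reply concerns size. A reader might infer that the true familywise error is simply 11–14%. The documents do not support that: it is the worst case, requiring 2.5 mg/kg to work and all three lower doses, including 1.5 mg/kg, to be exactly null. A reader might also infer that an inactive dose would be named the MELD that often. The two-sided figures include doses significantly worse than placebo, and the sample size section describes all tests as superiority tests, so such a dose is not a credible MELD. The benefit-only column is the better guide to that harm. Both points stand and limit the finding. Neither restores the claim, because the methods text speaks of a significant difference, the tests are declared two-sided, and the benefit-only rates still exceed 2.5% when two or more lower doses are null.

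Interim choice of middle doses might be thought to add further inflation. The choice rests on committee consensus combining clinical opinion, safety, T-cell counts and a Bayesian prediction, so the documents do not give a rule from which to compute it, and no figure is offered.

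It can also be said that this is phase 2, that the 2.5 mg/kg test is itself valid at 5%, and that a detailed SAP is promised before database lock. All true. A phase 2 trial may choose not to adjust, but it should not then claim 5% control. This is a stated property that is false, not a detail left for later.

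Finally, the Objectives section and the methods section might be read as contradictory, since one seeks the lowest effective dose among all doses studied and the other only below 2.5 mg/kg. This is a wording gap: the methods section is silent on what is concluded if only 2.5 mg/kg succeeds. It needs a sentence, and it is not evidence for the error-rate point.

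**Conclusion.** The concern holds. The stated rule is not a closed test, and the 5% familywise claim is wrong in both places. Two-sided familywise error is up to about 11–14% with 2.5 mg/kg effective and three null lower doses, about 8% with two null at the design effect, and at most 5% with one null or with 2.5 mg/kg null. For false findings of benefit the figures are about 6.7% and 4.7% (three and two null), against 2.5%.

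These rest on SD 0.27, 32 participants on placebo and on 2.5 mg/kg, and an assumed split of the remaining 50, which changes the results little. They ignore interim selection and dropout. The 2.5 mg/kg comparison is unaffected. The fault lies in the dose-finding half of the primary objective and in what is claimed for it.

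**What to change.** Keep the 2.5 mg/kg gate. Test the lower doses with Holm or step-down Dunnett at an overall 5%. Declare the MELD as the lowest rejected dose whose estimate favours ATG. Reconcile the Objectives and methods sections on what is concluded if only 2.5 mg/kg is significant.

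The cost is power. At Holm's first step (0.05/3 = 0.0167), 30 versus 32 participants and effect 0.20, power falls from about 82% to 67%, so the 80% middle-dose figure must be restated.

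A fixed descending sequence (1.5, then 0.5, then 0.1 mg/kg) also controls error and spends no alpha per test, but it relies on a monotone dose response and suffers if a higher middle dose has few participants. With a 6/38/6 split, 2.5 mg/kg at 0.22, and 1.5 and 0.5 mg/kg both at 0.20, the chance of declaring 0.5 mg/kg effective is 81% under the current rule, 71% with Holm and 34% with the sequence. The small 1.5 mg/kg arm (6 versus 32) has only about 37% power and blocks the path.

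If the sponsor prefers no adjustment, delete the closed-test and 5% familywise statements from both sections and say that the error rate can reach about 11–14%.

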### Statistical methods for secondary analyses

The secondary endpoints measured repeatedly over time will be analysed via a mixed effects model. Within the model time and categorical dose will be fixed effects along with an interaction term between time and dose with participant as a random effect. If required, the models may include additional covariates which may be potential factors that are confounding the relationship between dose and outcomes. The main additional covariate will be age of diagnosis. Subgroup analyses will be considered for a select list of potential covariates, the subgroup treatment effect will be analysed using an interaction test and additional factors will be included in the model to conduct this test. As an extra sensitivity analysis, we will assume a linear effect of dose and rerun the model with that assumption. A detailed statistical analysis plan will be produced before the final database lock.

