1. To determine the effects of ATG treatment on stimulated C-peptide	1. The area under the stimulated C-peptide response curve over the first 2 hours of an MMTT measured throughout the study in different ATG dosage groups	1. Baseline, 3, 6, 12 months
2. To determine the effects of ATG treatment on HbA1c	2. HbA1c measurements measured throughout the study in different ATG dosage groups in mmol/mol	2. Baseline, 3, 6, 12 months
3. To determine the effects of ATG treatment on intermittent CGM measures	3. CGM measures (time in range, time above, time below) measured throughout the study in all different ATG dosage groups and placebo	3. For 14 days at 3, 6, 12 months
4. To determine the effects of ATG treatment on fasting and stimulated DBS C-peptide measurements	4. DBS C-peptide measurements measured throughout the study in all different ATG dosage groups and placebo in pmol/L at 0 min and 60 min	4. Baseline, monthly
5. To determine whether ATG treatment mediates a reduction in CD4-positive T cells but relative preservation of CD8-positive T cells	5. CD4-positive T cells and CD8-positive T cells measured throughout the study in different dosage groups	5. Baseline, 1, 2, 4 weeks and 3, 6, 12 months
6. Descriptive analysis of the safety profile of different doses of ATG in different age groups	6. Safety will be assessed at each visit by physical examination, including assessment of the most commonly reported reactions to ATG, namely serum sickness, CD4 + lymphocyte decrease, cytokine release syndrome, fever, influenza-like symptoms and rash; vital signs (temperature, blood pressure, heart rate); weight, abnormal laboratory parameters (liver, kidney function, full blood count); reporting of adverse events in different dosage groups	6. Baseline, treatment day 1 and 2, 1, 2, 4 weeks and 3, 6, 12 months
7. To determine the effects of ATG treatment on T1D-associated autoantibodies (GADA, IAA, IA-2A and ZnT8A)	7. T1D-associated autoantibodies (GADA, IAA, IA-2A and ZnT8A) at the start and end of the study	7. Screening, 12 months
8. To determine the effects of ATG treatment on insulin requirements	8. Insulin requirements measured throughout the study in all different ATG dosage groups	8. Baseline, 1, 2, 4 weeks and 3, 6, 12 months
Exploratory objectives		

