These results will be used in conjunction with the C-peptide modelling which will be a Bayesian model of ln(AUC C-peptide +1). Only vague priors will be used in the model. The model will include fixed effects for categorical time and dose level along with an interaction term between time and dose and a random effect for participant. This model will be used to calculate the predictive probability that the mean ln(AUC C-peptide +1) is different from placebo for each dose level (including 2.5 mg/kg) given that the remaining participants to be allocated to the middle dose are given this dose level. If no such dose level is found then the next cohort of participants will be allocated to the 2.5 mg/kg dose level (improving power). Other stopping boundaries are not considered because the interim analyses are based on a mixture of incomplete follow-ups and fully observed follow-ups and subsequent analyses may suggest a middle dose not equal to 2.5 mg/kg. There is no sequential hypothesis testing done on the primary analysis.

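### The interim C-peptide model and the secondary mixed models, as written, carry no baseline term, so their dose contrasts are less precise than the collected data allow

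*Protocol article*

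**What the plan says.** All references are to the protocol article.

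- **Primary model** (Statistical methods for primary analyses): time, categorical dose, their interaction, a random participant effect, and "the baseline measurement of MMTT AUC C-peptide (transformed using the ln(x+1) function").
- **Secondary models** (Statistical methods for secondary analyses): "Within the model time and categorical dose will be fixed effects along with an interaction term between time and dose", with a random participant effect. Further covariates are optional, and the main one named is age at diagnosis.
- **Interim C-peptide model** (Interim analyses): "The model will include fixed effects for categorical time and dose level along with an interaction term between time and dose", with a random participant effect and vague priors. It yields the predictive probability that a dose's mean ln(AUC+1) differs from placebo. It uses all MMTT C-peptide results from all earlier cohorts.
- **Interim CD4/CD8 model** (same section): dose, nominal days and their interaction, with outcomes at 1, 2, 4 and 12 weeks. It estimates dose-placebo differences, but the intervals are then read as showing change, or none, from baseline.
- **Missing-data section** (Procedure to account for missing or spurious data): describes the repeated-measures model for the primary endpoint again, without a baseline covariate, and includes every available MMTT measurement.

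Table 1 lists baseline as a time point for stimulated C-peptide, HbA1c ("HbA1c measurements measured throughout the study in different ATG dosage groups in mmol/mol"), dried-blood-spot C-peptide, CD4/CD8 cells and insulin requirement. CGM is listed at 3, 6 and 12 months only.

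**The concern.** The primary model has a baseline term; the parallel models lack it. A random participant effect does not replace it. It describes the correlation among one person's measurements, but when every dose has its own mean at every visit, including baseline, the fitted 12-month difference with complete data is simply the raw difference in means.

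Two things are at stake. Secondary estimates are wider than they need be. And at an early interim, a chance difference in baseline C-peptide between small arms passes into the dose-placebo contrast shown to the Dose Determining Committee, whereas the final analysis would remove it. A later SAP need not repair this: it is promised before final database lock, while the six interims choose doses during recruitment.

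**Working it through.** **Inputs.** From the sample size section: SD "at 12 months was 0.27 nmol/L/min", effects of 0.22 (2.5 mg/kg) and 0.20 (middle doses) on the ln(AUC+1) scale, and "All tests are superiority tests and the tests are two-sided tests". From the design section: 30/5 = 6 per arm in cohort 1, 12/4 = 3 in cohorts 2 and 3, and 15/3 = 5 in cohorts 4 to 7. The correlation r between baseline and 12 months is not in the document, so a range is assumed.

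**The plan's own figures.** It states: "With this SD, 90% power, and 5% significance level, then 32 participants per arm will be needed to detect a change of 0.22 nmol/L/min". By the normal approximation, n = 2 × (1.960 + 1.282)² × 0.27² / 0.22² = 31.65, hence 32, as stated. For the middle doses, "there would be 80% power if there were 30 participants"; the t-test gives 80.5%. The SD is therefore used consistently, and nothing below changes these figures.

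**Standard error at 6 versus 6, complete data.**
- Unadjusted: 0.27 × √(1/6 + 1/6) = 0.156.
- Baseline-adjusted: 0.156 × √(1 − r²).
- Change from baseline: 0.156 × √(2(1 − r)).

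Generalised least squares for visits at 0, 3, 6 and 12 months with equal correlations shows what happens when baseline is one of the responses:

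| Assumed r | Baseline a response, free dose effect | Change from baseline | Baseline covariate, or equal baseline means | Variance saved, last versus first |
|---|---|---|---|---|
| 0.3 | 0.156 | 0.184 | 0.149 | 9% |
| 0.5 | 0.156 | 0.156 | 0.135 | 25% |
| 0.7 | 0.156 | 0.121 | 0.111 | 49% |

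The change contrast removes imbalance but gains precision only if r exceeds 0.5.

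**Incomplete follow-up.** Interims will mix complete and incomplete follow-up. As an illustration, suppose that in each arm of 6, three participants have reached 12 months, two 6 months and one 3 months. The free-dose-effect model gives 0.211, 0.199 and 0.184 at r = 0.3, 0.5 and 0.7, and the equal-baseline model gives 0.206, 0.183 and 0.148. The variance saved is 5%, 15% and 35%: smaller, but not nil.

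**Cost of estimating the slope.** With 30 participants in five arms there are 25 within-arm degrees of freedom. One covariate inflates the expected variance by about 1 + 1/(25 − 1 − 1) = 1.04. At r = 0.3 the factor 0.91 becomes about 0.95, still a gain.

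**Chance imbalance.** The difference in baseline means between two arms of n has SD √(2/n) in baseline SD units, ignoring age stratification. It exceeds 0.5 SD with probability 39% at n = 6 and 54% at n = 3. An imbalance of that size shifts the unadjusted contrast by 0.5 × r × 0.27 = 0.04, 0.07 or 0.09 at r = 0.3, 0.5 or 0.7, against a target of 0.20.

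**Ranking two doses of 6.** The chance that a dose with true effect 0.20 ranks below a dose with none is Φ(−0.20/SE). That is 10.0% unadjusted, and 8.9%, 6.9% or 3.6% adjusted at r = 0.3, 0.5 or 0.7.

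**The case against.** The strongest reply is that this is a condensed article and that covariates of secondary models are normally settled in the SAP. The secondary section leaves room for covariates and does not exclude baseline. That is fair, and it limits the secondary part to a recommended improvement. It carries less weight for the interim model, whose terms are listed and which is used before the SAP is due, although the committee charter may add detail.

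A second reply is that baseline C-peptide probably enters as a response, since all MMTT measurements are used. If baseline means were then held equal across arms, the adjusted standard errors above would follow. This is correct, so a flat statement that the models fail to adjust would go too far. But neither that constraint nor a baseline covariate is stated, and the listed dose-by-time interaction leaves baseline means free.

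A reader might infer that chance imbalance in arms of 3 to 6 drives dose selection. The document does not support that. Data pool over cohorts: placebo and 2.5 mg/kg reach 6, 9, 12, 17, 22 and 27 participants at the six interims. The model only advises. The committee must reach full consensus, weighs clinical opinion and safety, and cannot take forward a dose that leaves CD4 and CD8 counts unchanged. Arms of 3 to 6 describe the first interim and little-used middle doses.

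A reader might also infer bias. Omitting baseline does not bias a randomised contrast on average; it makes it noisier.

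**Conclusion.** The point holds as a loss of precision in the interim C-peptide model and the secondary models as written. With complete data at 6 versus 6, adjustment would cut the variance of the 12-month contrast by 9% to 49% for r between 0.3 and 0.7, less about 4% inflation for one estimated slope. With incomplete follow-up the gain is smaller. The effect on middle-dose choice is an influence, greatest at the first interim and for newly added doses.

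The result rests on r, which is undocumented; on equal correlations between visits; and on reading 0.27 as the unadjusted SD at 12 months. If 0.27 is already a residual SD, the unadjusted standard errors would be larger than shown.

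The 2.5 mg/kg test, the declaration of a minimally effective dose and the sample size are unaffected if the primary-analysis section governs. The missing-data section describes that same model without baseline, so the two must be aligned. The point does not extend to CGM, which has no baseline value. It is a worthwhile, inexpensive improvement and does not threaten the trial's validity.

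**What to change.** - In Statistical methods for secondary analyses, and for both the C-peptide and CD4/CD8 models in Interim analyses, add the endpoint's own baseline value as a covariate (ln(AUC+1) for C-peptide) wherever one is collected. Equivalently, keep baseline as a response and constrain its mean to be equal across arms, which fits the stated intention to use all MMTT measurements.
- Align Procedure to account for missing or spurious data with Statistical methods for primary analyses, so that the primary model is described once, with baseline.
- Fix the interim wording before the next interim, in the protocol or the committee charter, and do not leave it to a SAP due at database lock.

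The cost is wording, a small change to the analysis code and a few degrees of freedom: one for a common slope, more if the slope may differ by visit. No new data are needed.
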